### Qualitative analysis

Audio recordings of semi-structured interviews will be transcribed and imported into NVivo software^55^ and analysed as a combined dataset using a qualitative descriptive approach.^56^ This aims to describe manager, frontline staff, patient and family experiences of the intervention and implementation strategies.^57^ This will be triangulated with content analysis of observational field notes to describe relevant contextual features including comparisons across wards which may help to explain outcomes. Iterative analysis consultation with the wider investigative team will be used to critique and refine emergent results.^58^

### Economic analysis

A trial-based economic evaluation will be conducted from a hospital perspective and the time horizon will be limited to the trial duration. The comparator will be usual care. All intervention implementation and delivery costs (from study records), including staff and equipment costs, and all health service utilisation costs (from hospital records) during the trial period (pre-implementation, implementation and follow-up periods) will be used for the analysis. We will calculate the incremental cost per fall prevented of the intervention periods compared with control periods.

Principles of economic evaluation alongside stepped wedge trials will be followed.^59^ Bootstrapping will estimate a distribution around costs and health outcomes and calculate the CIs around the incremental cost-effectiveness ratios. The results will be plotted on the cost-effectiveness plane. A cost-effectiveness acceptability curve will be created to explore the uncertainty around the probability that the intervention is cost-effective, when considering a decision maker’s willingness to pay for falls prevented. All analyses will be undertaken in Stata V.16 (Stata, College Station, TX, USA). The results of the cost-effectiveness analysis will be reported following the consolidated health economic evaluation reporting standards statement.^60^

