### Sample size

Our design will provide 80% power to detect a 25% lower fall rate for intervention compared with the control phases (IRR=0.75), using a significant level of α at 0.05. Sample size calculations used the method described by Hemming and Taljaard^37^ with coefficients from previous studies^6 8^ and data from our partner organisations. To determine the appropriate sample size for the complete stepped-wedge design, we used the Stata function “steppedwedge”^38^ following the Hussey and Hughes approach,^39^ and conservatively assumed an intra-cluster correlation of 0.007.

The primary outcome is the falls rate (falls per 1000 bed days). Based on partner organisations’ monitoring data, we determined that 30 beds per ward for three steps and four clusters per sequence will result in 14 400 bed days in four wards for 120 days (3 months), providing >80% power.^38^,^40^ An estimated 5808 patients are expected to be admitted to the study wards during the study period.

Sample size calculations for the pre-implementation and post-implementation surveys were based on paired t-tests using survey data from our feasibility study. Assuming a SD of 0.8, the proposed sample sizes will provide 80% power to detect a mean change of 0.5 points on the Likert scale, as measured by survey questions.

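### The ICER confidence interval is planned without condition, yet it has no valid finite form unless falls prevented is clearly above zero

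*Protocol article*

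**What the plan says.** The Economic analysis section of the protocol article defines its result as a ratio: "We will calculate the incremental cost per fall prevented of the intervention periods compared with control periods". For uncertainty, bootstrapping is to give a distribution for costs and outcomes and to "calculate the CIs around the incremental cost-effectiveness ratios". The section names no type of bootstrap interval and does not say what is reported if the replicates fall in more than one quadrant. Net monetary benefit is not mentioned.

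The same paragraph plans two further displays: "The results will be plotted on the cost-effectiveness plane" and "A cost-effectiveness acceptability curve will be created to explore the uncertainty around the probability that the intervention is cost-effective", the latter as a function of willingness to pay per fall prevented.

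The precision of the denominator can be read from the Sample size section: "Our design will provide 80% power" for an IRR of 0.75, "using a significant level of α at 0.05".

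**The concern.** The denominator of the ratio, falls prevented, can be estimated at or near zero, or below it. As it passes through zero the ratio passes through infinity and its sign stops being informative. A negative ratio can mean cheaper with fewer falls, or dearer with more falls. A method that sorts replicates by their ratio puts these opposite results side by side. Once the 95% interval for falls prevented includes zero, the valid confidence set for the ratio is unbounded, yet sorting replicates still returns two finite limits.

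At stake is the reading of one published interval. A negative lower limit would look like possible savings when it comes from replicates in which the programme cost more and falls rose.

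**Working it through.** **Plan's own figures.** The Economic analysis section gives no number to reproduce. In the Sample size section, 30 beds × 4 wards × 120 days = 14,400 bed days, as stated. The power cannot be reproduced uniquely because no baseline fall rate is given, so the stated 80% is taken at face value.

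**Step 1: precision of the falls effect.** Inputs: IRR 0.75, power 80%, alpha 0.05 (two-sided assumed).

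SE(log IRR) = −ln(0.75) / (1.960 + 0.842) = 0.2877 / 2.802 = 0.103.

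**Step 2: how often falls prevented is not clearly above zero.** This means that more than 2.5% of the sampling distribution of falls prevented lies at or below zero. With z = −ln(IRR)/SE, the chance is Φ(1.96 − z). The last column is Φ(−z), the share of replicates at or below zero when the estimate equals that IRR.

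| IRR | z | Chance not clearly above zero | Share of replicates ≤ 0 |
|---|---|---|---|
| 0.75 | 2.80 | 20% | 0.3% |
| 0.80 | 2.17 | 42% | 1.5% |
| 0.85 | 1.58 | 65% | 5.7% |
| 0.90 | 1.03 | 82% | 15% |
| 1.00 | 0 | 97.5% | 50% |

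At IRR 1.0 the 97.5% includes 2.5% of trials in which falls prevented is clearly below zero. There the set for the ratio is bounded, but it is no longer a price per fall prevented.

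**Step 3: sensitivity to the stated power.** At IRR 0.75 the chance in Step 2 is simply 1 − power. A Hussey–Hughes calculation with 12 wards, three sequences, four periods (assumed), 30 × 120 = 3,600 bed days per ward-period and ICC 0.007 gives power of 46%, 55%, 75% and 84% at assumed baselines of 4, 5, 8 and 10 falls per 1000 bed days. The chance would then be 54%, 45%, 25% and 16%.

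**Step 4: what the limits would look like.** Assumptions, none from the documents: 5 falls per 1000 bed days; 24 intervention ward-periods × 3,600 = 86,400 bed days, so 432 falls expected without the programme; incremental cost 200,000 (SE 50,000), independent of falls; SE(log IRR) 0.103. Percentile limits are compared with the Fieller set, which holds every ratio R with (C − R·E)² ≤ 1.96²(s_C² + R²·s_E²), where C and E are incremental cost and falls prevented. The set is unbounded when E/s_E is below 1.96 in absolute value.

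| Estimated IRR | Percentile limits | Fieller set |
|---|---|---|
| 0.75 | 814 to 5,596 | 827 to 5,239 |
| 0.85 | −16,332 to 24,086 | everything outside −16,760 to 1,130 |
| 0.90 | −39,656 to 44,150 | everything outside −4,984 to 1,350 |

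At 0.75 the two agree closely. At 0.85, mean falls prevented is 62.8 with SD 432 × 0.85 × exp(0.103²/2) × √(exp(0.103²) − 1) ≈ 38, so E/s_E ≈ 1.65 and the set is unbounded. The percentile interval then includes ratios near zero that the data exclude and leaves out large ratios that the data allow. Its negative tail is not savings: the chance of a negative cost difference is Φ(−200,000/50,000) = Φ(−4), under 0.01%. It comes from the 5.7% of replicates with more falls.

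**The case against.** The strongest reply is that the article does not specify the faulty method. Percentile, BCa and angular intervals on the plane all fit its wording, and angular ordering would not mix quadrants in the same way. The choice of interval type properly belongs in a fuller analysis plan, which is not shown. This stands: a reader might infer that percentile limits are planned, and the document does not say so. What remains is that an interval on the ratio is already fixed as an output with no condition. No type of bootstrap makes a finite interval valid when the correct set is unbounded.

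Second, the bootstrap distribution of costs and outcomes, the plane and the acceptability curve all remain valid near zero benefit, and no decision rule uses the ICER interval. This also stands. A reader might infer that the economic evaluation as a whole is unsound; the document does not support that. These outputs do not, however, correct an ICER interval printed beside them.

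Third, a reader might treat every ICER interval that crosses zero as faulty. That goes too far. When falls prevented is clearly positive, a change of sign reflects genuine uncertainty about cost.

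Fourth, coverage is not generally poor. In repeated sampling under the Step 4 assumptions (2,000 trials per scenario), percentile intervals covered the true ratio in 98%, 97%, 97% and 95% of trials at IRR 0.75, 0.85, 0.90 and 0.95, falling to 84% at 0.98. At moderate effects the trouble is therefore chiefly what the limits mean.

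**Conclusion.** The point holds as a minor one on a secondary economic output. The plan commits without condition to a confidence interval on cost per fall prevented. If falls prevented is not clearly above zero, limits from sorting replicates by ratio are uninterpretable, and no finite interval is valid. On the stated power this would arise in about one trial in five even if the design effect is true, and in most trials if the true reduction is 15% or less.

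These frequencies rest on a two-sided 5% level, a normal approximation for log IRR and the stated 80% power. The monetary illustration rests on assumed costs and an assumed baseline rate. The documents do not support saying that the planned interval will be meaningless: when benefit is clear it is acceptable and close to Fieller.

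**What to change.** In the Economic analysis section, or in the full economic analysis plan before analysis starts:

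- Report mean incremental net monetary benefit (willingness to pay × falls prevented − incremental cost) with its bootstrap 95% CI over a stated range of willingness to pay per fall prevented.
- Keep the ICER point estimate, the cost-effectiveness plane and the acceptability curve.
- Report an ICER interval, with its type named, only when at least 97.5% of replicates show falls prevented above zero.

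The cost is a sentence or two. The same replicates serve, no new data are needed, and the willingness-to-pay framing is already in the section.

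There are two downsides. Readers who expect an ICER interval may get a net-benefit interval instead. Also, an ICER interval shown only after a clear falls result is selected on that result. Under the Step 4 assumptions, its coverage in the trials where falls prevented was clearly above zero was 1,578/1,619 (97%) at IRR 0.75, 657/715 (92%) at 0.85 and 289/341 (85%) at 0.90. The net-benefit interval, reported in every case, should therefore be the main statement of uncertainty.

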### Trial monitoring and access to data

The trial investigators meet at least bimonthly to discuss the trial progress. The investigators will adhere to routine HREC reporting. A data safety and monitoring board (DSMB) has been established for this study with members independent to the study. The DSMB will convene in the event of an unanticipated serious adverse event that could be related to the intervention occurring during the trial. The DSMB charter can be accessed at request by contacting the research team.

All electronic study data will be stored on the sponsor’s secure password-protected servers, primarily the research electronic data capture server. Data linkage will be used for the coded hospital medical record and incident management system data to protect the privacy of individuals. Only de-identified data will be used for analysis. Strict privacy protection measures will be implemented to safeguard the confidentiality of individuals’ information. Data will only be accessed by approved members of the research team. All study data will be retained securely for a period of 15 years after study completion.

## Ethics and dissemination

The Human Research Ethics Committee (RPAH Zone) of the Sydney Local Health District has approved this trial (protocol number X24-0087 and 2024/ETH00583). Updated procedures will only be implemented once they have been reviewed and approved by an Ethics Committee (or if applicable a governance office) for each site. Data collection commenced in October 2024 and is due for completion in May 2026. Results from the trial intend to be published in international journals and presented at relevant conferences.
